#### Phase II primary endpoint analysis

##### Primary analysis

Treatment effects and 95% confidence intervals on response at 4 weeks will be estimated from multivariable mixed-effects logistic regression, including the minimisation factors and treatment group as fixed effects and centres as random effects. Simple contrasts for each treatment strategy compared with the TAU arm will be used.

#### Phase II secondary endpoint analysis

AEs and SAEs that are classified as expected and related to DFUs and trial treatment strategies, or RUSAEs will be summarised by treatment group.

Mean per-patient costs of treatment, healthcare use and total resource use, together with a measure of variance will be reported by treatment group.

#### Phase III primary endpoint analysis

##### Primary analysis

The hazard ratios for the phase III endpoint will be estimated using Cox proportional hazards regression with covariates for the minimisation factors, treatment arm (fixed effects) and centre (random effects) and stratification for the phase in which the participant was recruited.

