Box 1Inclusion and exclusion criteria**Inclusion criteria**Aged ≥18 years.Diagnosis of diabetes mellitus (according to WHO criteria).^47^Has a chronic diabetic foot ulcer (DFU) or surgical debridement wound or open minor amputation and in the opinion of the attending clinical team is not on a healing trajectory despite usual best care for a minimum of 4 weeks since initial presentation at the multidisciplinary team (MDT) DFU service.*The index DFU has an area ≥0.8 cm^2^.Ankle brachial index for the leg of the index ulcer ≥0.7 or non-compressible (measurements available in the participants notes taken within 3 months of randomisation can be used if no change in intervention or vascular events have occurred).Expected to comply with the treatment strategies and follow-up schedule.Consent to foot and wound photography.Consent to participate (written/witnessed verbal informed consent).**Exclusion criteria**Has any current clinically infected DFU on the foot of the index ulcer (as per Infectious Diseases Society of America (IDSA) guidelines).^48^Glycated haemoglobin (HbA1c)>110 mmol/mol (measurements available in the participants notes taken within 3 months of randomisation can be used if no change in intervention or vascular events have occurred).Estimated glomerular filtration rate (eGFR) <20 mL/min/1.73 m^2^ (measurements taken within 3 months of randomisation can be used if no change in intervention or vascular events have occurred).Index ulcer duration >2 years.Planned or previous treatment with corticosteroids to an equivalent dose of prednisolone >10 mg per day or other immunosuppressive/immunomodulating therapy within 4 weeks prior to randomisation.Has evidence of connective tissue disorders as a cause of ulceration (eg, vasculitis or rheumatoid arthritis).Has evidence of dermatological disorders as a cause of ulceration (eg, pyoderma gangrenosum or epidermolysis bullosa).Planned or previous growth factor treatment within 4 weeks prior to randomisation.Planned or previous revascularisation or foot surgery affecting healing on the foot of the index ulcer within the 4 weeks prior to randomisation.Index ulcer base has bone or joint involvement.Previously received decellularised dermal allograft (DCD) for the index ulcer within 4 weeks prior to randomisation.Previously received negative pressure wound therapy (NPWT) for the index ulcer within 4 weeks prior to randomisation.Previously received hydrosurgical or surgical debridement for the index ulcer within 4 weeks prior to randomisation.Has previously been randomised to the Multiple Interventions for Diabetic Foot Ulcer Treatment Trial (MIDFUT) Study.Unable to receive one or more of the randomised treatment strategies for any reason at the discretion of the attending clinical team (eg, risk of excessive bleeding, serious falls risk, known allergies to NPWT dressings or dCELL dermis preparation components).*Defined as failure to achieve >50% reduction in index ulcer area over a minimum of 4 weeks using local wound measurement policies.

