### Randomisation

Following confirmation of eligibility, consent and completion of baseline assessments, participants will be randomised. In phase II, randomisation will be in a 1:1:1:2 allocation ratio to the three treatment strategies and TAU group, respectively, as an approximation to Dunnett’s recommendation.^22^ In phase III, randomisation will be in a 1:1 allocation ratio to one treatment strategy and TAU. Randomisation in both phases will use a minimisation algorithm, incorporating a random element, via a central 24 hours automated telephone or internet randomisation system, based at the Leeds Clinical Trials Research Unit (CTRU). The dynamic allocation method will ensure the groups are well balanced for:

Centre.Aetiology (neuropathic or neuro-ischaemic).Index ulcer duration (<6 months, ≥6 months).Anatomical site (forefoot, midfoot/hindfoot).Presentation (DFU, surgical debridement wound, open minor amputation).

In addition, at the time of randomisation, 25% of participants will be randomly selected to have photographs of the index ulcer taken, if it is unhealed, at weeks 12, 20 and 52, for central blinded review.

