### Assessments/data collection and follow-up

#### Baseline assessment

Participant demographics including date of birth, gender, ethnicity, NHS number and site of the index ulcer will be recorded.

Clinical history will be recorded including smoking history, duration and type of diabetes, number of ulcers and index ulcer characteristics, for example, first or recurrent ulcer, aetiology, existing wound therapies and Site, Ischaemia, Neuropathy, Bacterial Infection and Depth (SINBAD) classification.^24^ Initial index ulcer area tracing (using acetate) will also be obtained. Participants will be asked to complete quality of life questionnaires: DFS-SF and EQ-5D-5L.

Randomisation and application of the treatment strategy will take place after baseline assessments and questionnaires have been completed, on the same day.

Information collected post-treatment will include details of the treatment strategy applied to the index ulcer and to any other ulcers on the foot of the index ulcer, and expected AEs and serious AEs (SAEs). Post HD debridement, index ulcer area acetate tracing and photographs will be obtained.

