### Sample size

The planned maximum sample size is 447 participants, 245 participants in phase II and 202 participants in phase III. The apportionment of participants to phase II and phase III was estimated using a series of simulation studies.

In phase II, 49 participants per treatment strategy arm and 98 participants in the TAU arm will be recruited. The target effect size in phase II is an absolute increase of 25% in the proportion of participants achieving at least a 50% reduction in wound area by 4 weeks post randomisation, assuming 39% reach at least a 50% reduction by week 4 in the TAU arm (local audit data) and 64% achieve this outcome in the treatment strategy arms.

An additional 101 participants will be recruited into each arm evaluated in phase III, corresponding to a total (phase II and III combined) of 150 in the remaining treatment strategy group and 199 in the TAU arm (total of 349 participants for evaluation in phase III).

The minimum clinically important effect size in phase III is a hazard ratio (HR) of 1.5, assuming a median time to healing of 21 weeks for the TAU arm (local audit data) and 14 weeks for the treatment strategy arms^18 27–30^ and 18.0% and 7.6% *un*healed at 52 weeks in the TAU and treatment strategy groups, respectively (assuming exponential distribution for time to healing).

Several scenarios for the power of the trial have been considered. In all cases a 10% loss to follow-up by 4 weeks and 25% loss to follow-up by 52 weeks is assumed. In the case where there is a single effective treatment strategy arm, the design has 83.9% power to recommend a truly effective treatment strategy (ie, for it to progress from phase II and for a significant result found at phase III). A treatment strategy group that progresses to phase III and which is significantly better than TAU at the two-sided 4% significance level (to control the familywise error rate at 5%) on the time to healing endpoint will be declared clinically effective.

A formal sample size review will be conducted at 52 weeks, after 220 participants have been recruited, to re-estimate the proportion of participants lost to follow-up by 52 weeks post randomisation and the final sample size. The review will allow the overall loss to follow-up to be estimated to a minimum precision ±5.7% (corresponding to half width of the 95% CI), assuming a maximum loss to follow-up of 25%.

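### The phase III primary Cox model leaves out baseline index-ulcer area, which is traced before randomisation; adding it costs nothing and may gain precision

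*Protocol article*

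**What the plan says.** - **Phase III model** (Phase III primary endpoint analysis, Primary analysis): "Cox proportional hazards regression with covariates for the minimisation factors, treatment arm (fixed effects) and centre (random effects"), with stratification for the phase of recruitment.
- **Minimisation factors** (Randomisation): centre and aetiology, followed by "Index ulcer duration (<6 months, ≥6 months).Anatomical site (forefoot, midfoot/hindfoot).Presentation (DFU, surgical debridement wound, open minor amputation"). Index-ulcer area is not listed.
- **Measurement** (Baseline assessment): "Initial index ulcer area tracing (using acetate) will also be obtained". On timing: "Randomisation and application of the treatment strategy will take place after baseline assessments and questionnaires have been completed, on the same day". The same section has a further tracing taken after hydrosurgical debridement (HD).
- **Eligibility** (Box 1): "The index DFU has an area" of at least 0.8 cm². No maximum area is given.
- **Endpoint** (Healing and reulceration assessments): healing means full re-epithelialisation without drainage, confirmed at two blinded assessments two weeks apart.
- **Phase II model** (Phase II primary endpoint analysis): the same covariates, "including the minimisation factors and treatment group as fixed effects and centres as random effects".
- **Prognostic factors**: left to an exploratory Cox model with no candidate factors named.

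**The concern.** The covariate set is written out, so this is not a matter the article leaves open. It omits a baseline measurement that has a plain link to the endpoint: for complete closure, a larger ulcer has more surface to re-epithelialise, and nothing caps ulcer size at entry.

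In a Cox model, omitting a prognostic covariate pulls the treatment HR towards 1 relative to the HR conditional on that covariate, even under perfect randomisation. Adjusting usually raises power. Area is also outside the minimisation, so a chance difference in ulcer size between 150 and 199 participants would pass straight into the primary HR, and into the cumulative incidences at 12, 20 and 52 weeks taken from the same model. At stake are the precision of the definitive comparison and its robustness near the 4% threshold.

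**Working it through.** **Inputs from the article (Sample size):** 150 participants on the continued strategy and 199 on treatment as usual (TAU); medians 14 and 21 weeks; HR 1.5; 25% loss by 52 weeks; two-sided 4% level; stated power 83.9% to progress from phase II and then be significant in phase III.

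**Input not in the article:** the prognostic strength of baseline area. Assumed range: healing HR of 1.0 to 2.0 per SD of log area.

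**1. Reproducing the plan's figures, with no area term**
- HR = 21/14 = 1.50.
- Unhealed at 52 weeks = 2^(−52/21) = 18.0% and 2^(−52/14) = 7.6%. Both match.
- Healing rates: ln2/21 = 0.0330 and ln2/14 = 0.0495 per week. Dropout rate: −ln(0.75)/52 = 0.00553 per week.
- P(event) = λ/(λ+δ) × [1 − exp(−52(λ+δ))] = 0.741 (TAU) and 0.848 (strategy).
- Events = 199 × 0.741 + 150 × 0.848 ≈ 275.
- Schoenfeld: √(275 × 0.430 × 0.570) × ln1.5 − 2.054 = 3.327 − 2.054 = 1.273, so phase III power is about 90%.
- Joint simulation of phase II selection followed by a phase-stratified log-rank test: 83.6% to 84.4%, depending on the assumed correlation between response and healing. The stated 83.9% is reproduced without any area covariate.

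**2. Simulated Cox models with and without area**

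Healing was exponential given log area, with the TAU median calibrated to 21 weeks, dropout as above and 150 v 199 participants. There were 2,500 runs per setting with 1.5 as the area-adjusted HR, and 1,500 with 1.5 as the arm-level HR. Monte Carlo error is about one point or less.

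| HR per SD of log area | 1.5 is the arm-level HR: power without / with area | 1.5 is the area-adjusted HR: HR without area | 1.5 is the area-adjusted HR: power without / with area |
|---|---|---|---|
| 1.0 | 90% / 90% | 1.50 | 90.5% / 90.5% |
| 1.25 | 89% / 90% | 1.49 | 88.7% / 90.4% |
| 1.5 | 90.5% / 94.7% | 1.45 | 83.4% / 89.4% |
| 2.0 | 89.8% / 98.3% | 1.38 | 71.2% / 88.8% |

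Neither reading keeps every planning input once area matters. The area-adjusted reading keeps the 14-week median, but at 2.0 per SD it leaves 23.5% and 14.1% unhealed at 52 weeks. The arm-level reading needs an area-adjusted HR of 1.669 at 2.0 per SD, so the strategy median becomes 21/1.669 = 12.6 weeks.

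**3. Chance imbalance**

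The SD of the between-arm difference in mean log area, in SD units, is √(1/150 + 1/199) = 0.108, if the minimisation factors do not balance area indirectly. A 1.96-SD imbalance is 0.212 SD. It shifts the HR by about 1.25^0.212 = 1.05, 1.5^0.212 = 1.09 or 2.0^0.212 = 1.16.

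**The case against.** The strongest objection is that nothing here is an error. The planned HR of 1.5 comes from arm-level curves, and the stated power reproduces without area. Randomisation protects the type I error, and an HR adjusted only for the allocation factors is legitimate. All of this stands. A reader might infer that the omission biases the HR or makes the 83.9% wrong; the documents do not support that. The 71% figure arises only if 1.5 is taken as conditional on area, which departs from the plan's own 52-week percentages.

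Second, no passage says that baseline area predicts healing, or how strongly. The Introduction cites area reduction at 4 weeks, which is a different variable. This also stands: the size of the gain is assumed, and at 1.25 per SD it is at most about two points. The simulations also leave out the planned covariates, so any prognostic information that aetiology, duration, site, presentation or centre shares with area would shrink the gain.

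Third, a reader might infer that the phase II go/no-go decision is compromised. It is not. Box 2 compares point-estimate proportions with a 10-point margin, and adding area to the logistic model would not change them as written. The endpoint, at least a 50% reduction, is also already relative to starting area. Nor do the documents show that the infection, reulceration or quality-of-life models need area.

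Finally, the full protocol or the SAP may add covariates. That does not alter the set stated here, which is specific and excludes area.

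**Conclusion.** The point holds as an efficiency recommendation for the phase III primary Cox model. The stated covariates omit a pre-randomisation measurement that plausibly predicts complete closure. The benefit depends on an assumption. With 1.5 as the arm-level HR, adding area moves phase III power from about 90% to about 90%, 95% or 98% at 1.25, 1.5 or 2.0 per SD. With 1.5 as the area-adjusted HR, leaving area out costs about 2, 6 or 18 points. If area is not prognostic, there is no change. In no scenario computed did adjustment materially cost power. The omission and the direction of its effect are certain if area is prognostic; the size is not known. The sample size and the validity of the planned analysis are not in question.

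**What to change.** Before any unblinded phase III analysis, prespecify log(index-ulcer area from the initial pre-treatment tracing) as a continuous covariate in the phase III primary Cox model, alongside the terms already listed.

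Use the pre-randomisation tracing in all arms. Never use the post-HD tracing: it follows treatment, and HD is part of every strategy arm but not of TAU.

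State a simple imputation for a missing or unusable baseline tracing. The photograph backup described under Blinding concerns the week 4 tracing and should not be assumed to cover baseline.

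Adding area to the phase II logistic model is optional and does not affect the progression rule. The cost is a sentence or two in the analysis plan, with no new data and no change to the sample size.

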#### Phase III secondary endpoint analysis

Similar regression-based analyses will be used for other secondary endpoints. Cumulative incidence of healing at 12, 20 and 52 weeks post randomisation will be obtained from the primary endpoint analysis model. A Poisson-Gamma regression model will be fitted to infection status over time. A Cox proportional hazards regression model will be fitted to time to reulceration of the index ulcer on those participants where healing of the index ulcer is confirmed. A repeated measures, random coefficients, linear regression model will be fitted to the DFS-SF Score over time.

All AEs and SAEs, including amputations and admissions to hospital, will be recorded and summarised by treatment strategy received. Expected treatment-related AEs include: pain, bleeding and infection from HD; bleeding, infection and skin irritation/breakdown from NPWT; seroma and allergic reaction from DCD.

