The evidence for adjuvant therapies for DFU treatment was reviewed in NICE guideline NG19,^12^ which concluded that the quality of trials was poor due to binary and early endpoints and small sample sizes. It recommended that future trials are sufficiently powered, with outcomes including time to healing, incidence and extent of amputation (major or minor), ulcer recurrence, HRQoL, adverse events (AEs), hospital admissions and length of stay. These findings were supported by a review by the International Working Group on the Diabetic Foot.^21^

In summary, quality data on the outcome of adjuvant therapies for DFU is rare. A 30% increase in prevalence of disease is anticipated by 2035, which will add to the already substantial costs of treating DFUs, in a time of global fiscal uncertainty. With international guidance advocating the need for robust RCTs in this area,^21^ and technical advancements in three adjuvant therapy options (HD, DCD and NPWT), an RCT to compare treatment strategies is timely.

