#### Phase III secondary objectives

To compare one treatment strategy as an adjunct to TAU, continued from phase II, with TAU alone for:

Healing status of the index ulcer at 12, 20 and 52 weeks.Rate of ulcer infection in the foot of the index ulcer over 52 weeks post randomisation.Incidence of reulceration following healing of index ulcer over 52 weeks post randomisation.Quality of life using the Diabetic Foot Ulcer Scale—Short Form (DFS-SF) and the Five-level five-dimension EuroQol (EQ-5D-5L) over 52 weeks post randomisation.Incidence of AEs (including amputation, infection in any ulcer on the foot of the index ulcer and hospital admission) over 52 weeks post randomisation.Cost effectiveness over 52 weeks.

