### Statistical analysis

A statistical analysis plan for phase II and phase III final analyses will be finalised and signed off before any data analyses are conducted.

The complete case population will be used for the analysis of the phase II endpoint under the assumption that data are missing at random (MAR).^31^ A sensitivity analysis will be considered if there is differential missing endpoint data observed across treatment arms.

Phase III analyses will use intention to treat whereby participants will be analysed according to randomised treatment group. A per-protocol population will also be defined.

For phase III endpoint analyses, data from all participants recruited in phase II and phase III will be included.

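### Amputation and hospital admission belong to a comparative phase III secondary objective, yet are to be summarised by strategy received, against an intention-to-treat rule with no stated safety exception

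*Protocol article*

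**What the plan says.** Three statements in the protocol article bear on the same events.

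- **Phase III secondary objectives.** The list opens with "To compare one treatment strategy as an adjunct to TAU, continued from phase II, with TAU alone for", and one of its items is "Incidence of AEs (including amputation, infection in any ulcer on the foot of the index ulcer and hospital admission) over 52 weeks post randomisation". Amputation and admission are therefore part of a stated comparison of two groups.
- **Statistical analysis.** "Phase III analyses will use intention to treat whereby participants will be analysed according to randomised treatment group". The only other set named for phase III is per-protocol: "A per-protocol population will also be defined". No safety or as-treated set is mentioned, and no exception for adverse events is made.
- **Phase III secondary endpoint analysis.** "All AEs and SAEs, including amputations and admissions to hospital, will be recorded and summarised by treatment strategy received". This is the only analysis the article states specifically for adverse event incidence. The same section also has the general sentence "Similar regression-based analyses will be used for other secondary endpoints", without saying whether adverse event incidence is among those endpoints.

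For phase II, the secondary endpoint analysis groups safety events differently: "or RUSAEs will be summarised by treatment group".

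**The concern.** Read together, the general rule groups participants as randomised and the specific sentence groups them as treated. The difference matters little for bleeding at debridement or an allergic reaction to the graft, where the question is what happened to people who had the procedure.

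It matters more for amputation and hospital admission. The Introduction presents amputation as a consequence of infected ulcers. It also cites guidance that trials should report "outcomes including time to healing, incidence and extent of amputation (major or minor), ulcer recurrence, HRQoL, adverse events (AEs), hospital admissions and length of stay". Amputation and admission are disease outcomes on which a benefit or a harm of the strategy might be claimed, and only the randomised grouping protects such a claim from selection.

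Receipt can depart from allocation. The strategies are nested combinations, the graft needs a suitably prepared wound bed (Introduction), and the negative pressure therapy runs for two weeks (Interventions). If the reason a component was not given is linked to prognosis, a grouping by receipt mixes that reason into the comparison with TAU.

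**Working it through.** **Step 1: the texts side by side**

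| Section | Events | Grouping |
|---|---|---|
| Phase III secondary objectives | Adverse event incidence, naming amputation and admission | Selected strategy v TAU alone |
| Statistical analysis | Phase III analyses in general | Randomised group; no safety exception |
| Phase III secondary endpoint analysis | All adverse and serious adverse events, naming amputation and admission | Strategy received |
| Phase III secondary endpoint analysis | Infection over time | Poisson-Gamma model; no separate grouping given, so the general rule applies |
| Phase II secondary endpoint analysis | Expected related events and related unexpected serious events | Treatment group |

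Rows 2 and 3 conflict for the outcomes in row 1.

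**Step 2: what the conflict could do to the comparison**

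The article states no figure that can be reproduced here: it gives no rate of non-receipt and no amputation or admission risk. What follows is an illustration.

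Inputs:
- From Sample size: 150 participants allocated to the selected strategy and 199 to TAU.
- Assumed: a fraction q of participants are of the type who would not be given the strategy, in the same proportion in both arms. Their event risk is k times that of the others, whose risk is x. There is no true treatment effect. Non-receivers are counted with TAU, and nobody allocated to TAU receives the strategy.

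Formulas:
- Risk in either randomised group: R = x[1 + q(k − 1)], so the randomised risk ratio is 1.00.
- By-received strategy risk: x.
- By-received TAU risk: (199R + 150qkx)/(199 + 150q).
- By-received risk ratio: (199 + 150q)/{199[1 + q(k − 1)] + 150qk}. The baseline risk x cancels.

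Results:
- q = 5%, k = 2: 206.5/(208.95 + 15) = 0.92
- q = 5%, k = 3: 206.5/(218.9 + 22.5) = 0.86
- q = 10%, k = 2: 214/(218.9 + 30) = 0.86
- q = 10%, k = 3: 214/(238.8 + 45) = 0.75

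With x = 10%, q = 10% and k = 2, the by-received risks are 10.0% and 0.10 × 248.9/214 = 11.6%. Both randomised groups show 11.0%.

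**Step 3: how far this depends on the assumptions**

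- If q = 0 or k = 1, the ratio is 1.00 and there is no bias.
- If non-receivers are at lower risk, the direction reverses: q = 10%, k = 0.5 gives 214/(199 × 0.95 + 7.5) = 214/196.55 = 1.09.
- If non-receivers are recorded under some other strategy and leave the two-group comparison, the ratio is 1/[1 + q(k − 1)]. That gives 1/1.05 = 0.95 at q = 5%, k = 2 and 1/1.2 = 0.83 at q = 10%, k = 3.

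**Step 4: scale against chance**

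In the 10.0% v 11.6% case the by-received groups hold 135 and 214 people. The standard error of the difference is √(0.100 × 0.900/135 + 0.116 × 0.884/214) = 0.034. The shift of 1.6 percentage points is just under half of that.

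**The case against.** The strongest answer is that the specific sentence is a deliberate exception. Summarising safety events by treatment received is ordinary practice, and the sentence is followed directly by a list of procedure-related events. Safety sets are commonly defined in the analysis plan or the full protocol, which are not shown. For procedure-related events this stands. It does not settle amputation and admission, which the article names in the by-received summary and also lists under a comparative objective. The point rests on a grouping the article does state.

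Second, the sentence describes a summary, with no test or effect estimate. A reader might infer that the randomised comparison of these outcomes is broken or abandoned. The text does not support that: the general sentence on regression for other secondary endpoints leaves room for an intention-to-treat analysis of adverse event incidence, although it does not promise one.

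Third, non-receipt may be rare. Box 1 excludes patients who cannot have one or more of the strategies and gives bleeding risk as an example. Baseline assessment, randomisation and treatment fall on the same day. Early loss of a graft or of negative pressure therapy is recorded as compliance at weeks 1 and 2, and nothing says it changes the strategy received. A reader might also infer that someone missing a component is moved to TAU or to a dropped strategy; no section defines how partial receipt is classified. These points limit the likely size of any bias but do not remove the conflict.

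Fourth, infection in the foot of the index ulcer has its own objective and its own Poisson-Gamma model under the general rule. That is right, and infection needs no further analysis on this account.

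**Conclusion.** The point holds in a limited form. The article sets an intention-to-treat rule without exception, makes amputation and admission part of a comparative secondary objective, and then states only a by-received summary for them. Following that grouping can bias the comparison with TAU when non-receivers differ in risk.

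The size is unknown. The range of 0.92 to 0.75 rests wholly on assumed non-receipt of 5–10%, an assumed risk 2–3 times as high, and an assumed rule that non-receivers are counted with TAU. A reader might infer that the bias favours the strategy. That follows only if non-receivers are at higher risk, which the article does not establish. At the milder settings the shift is small beside sampling error, though unlike sampling error it would not shrink in a larger trial.

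The time-to-healing analysis, the power and the 4% significance level are untouched, as are the secondary endpoints with their own regression models.

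**What to change.** 1. In the phase III secondary endpoint analysis, state that amputation, hospital admission and serious adverse events are compared by randomised group, as the main presentation for the adverse event objective.
2. Keep by-received tables as a supplement for procedure-related events such as pain, bleeding, seroma and allergic reaction.
3. In the Statistical analysis section, name those by-received tables as the exception to intention to treat, and say how a participant who received only part of a combination is classified in them.

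The cost is a sentence or two and one more set of tables. No new data are needed, and neither sample size nor trial conduct changes.
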